#### Outcome 3: Cost avoidance.

A cost-only analysis will be performed. We will use the associated charges from a local publication on using a bottom-up micro costing approach to calculate the costs of X-rays for spine imaging, specifically the Cervical Spine X-ray at €68.22 and the Lumbar Spine X-ray at €79.85, to estimate cost avoidance [7]. From the dataset, we will estimate the CDSS potential cost avoidance using the formula: “Number of inappropriate imaging X cost of specific imaging”. Additionally, we will also illustrate the potential cost avoidance from the inappropriate imaging.

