**Fig 1 pone.0336801.g001:**
[figure not shown]
Flow chart and timeline of the study.

In the first phase for both groups, ED physicians will follow the usual clinical practice (“Do nothing”) of making imaging referrals without consulting CDSS. Both groups will be informed during their onboarding on the availability of imaging referral guidelines in the training handbook and also on the intranet. Specifically, the physicians in the control group will not receive any CDSS introduction/orientation and no additional imaging referral guidelines education beyond the standard onboarding process. Simultaneously, a retrospective analysis of the electronic medical records will be performed.

The study included consecutive patients referred to the ED’s radiology department for cervical and lumbar spine radiography by the cohort of recruited ED physicians. Patients who had imaging referrals from general practitioners will be omitted due to our lack of access to the clinical notes for this particular cohort. For each case, the initial clinical diagnosis (reasons for the referral), the ordered procedure, patient demographics (age and gender), and ED clinical notes will be collected. To enhance the accuracy of analysing each imaging referral, the initial clinical diagnosis will be integrated with the corresponding ED clinical notes, including signs, symptoms, clinical examination, and red flags. This integration will result in a more comprehensive “indication(s)” for the imaging procedure. The appropriateness of each imaging referral will be determined with reference to localised and institutional approved imaging referral guidelines built on imaging referral guidelines published by ACR, ESR and RCR (Refer to Table 1). The records will be archived to REDCap (Research Electronic Data Capture) hosted by SingHealth for subsequent analysis.

**Table 1 pone.0336801.t001:** Imaging referral guidelines* for X-ray Cervical and Lumbar Spine.

Procedure	Clinical condition	Appropriate Imaging Criteria

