#### Outcome 4: Radiation dose.

The established literature “Radiology: Patient Exposure from Radiologic and Nuclear Medicine Procedures in the United States: Procedure Volume and Effective Dose for the Period 2006–2016” will serve as the basis for estimating the radiation dose to patients [42]. The publication, based on the International Commission on Radiological Protection (ICRP) Publication 60, indicates an effective dose per scan of 0.36 mSv for X-rays of the Cervical Spine and 1.4 mSv for the Lumbar Spine. We will establish the cumulative effective dose associated with the imaging tests and highlight the comparison of the relative contributions of appropriate and inappropriate imaging with the total number of examinations and the total collective effective dose. We will also evaluate the number of imaging tests avoided (i.e., physician after consulting CDSS followed CDSS recommendations on not referring patient(s) for imaging) and the associated radiation dose prevented using the formula: “effective dose per scan X number of imaging avoided”.

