#### Outcome 5: Sustainability.

For this outcome, we will evaluate the impact of CDSS on environmental sustainability. Energy consumption and carbon emissions were approximated from established radiology literature (X-ray Cervical and Lumbar Spine – 0.91 kWh, 1.6 kg CO_2_e) [43–45].

Similar to the thread on radiation dose, we will compare the pre-implementation data on the volume of spine imaging referrals with post-implementation data of the same duration, focusing on the changes in the volume of the overall imaging utilisation before and after the interventions. We will estimate the carbon emissions and energy consumption reduction based on before vs. after implementation data. Similarly, we will also calculate the carbon emissions and energy consumption from imaging tests prevented, using the formula “carbon emissions/energy consumption X number of imaging avoided”.

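### Outcome 3 prices inappropriate X-rays that were ordered, so the CDSS cost-avoidance figure measures avoidable cost and not cost the CDSS avoided

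*Protocol article*

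**What the plan says.** Outcome 3 (Cost avoidance) takes unit costs from a local costing publication, "specifically the Cervical Spine X-ray at €68.22 and the Lumbar Spine X-ray at €79.85, to estimate cost avoidance". It continues: "From the dataset, we will estimate the CDSS potential cost avoidance using the formula", and the formula is "Number of inappropriate imaging X cost of specific imaging". A further sentence follows: "Additionally, we will also illustrate the potential cost avoidance from the inappropriate imaging". The section does not say which phase or which group supplies the count.

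The dataset is described under Comparator and intervention, in the text below Fig 1: "The study included consecutive patients referred to the ED’s radiology department for cervical and lumbar spine radiography by the cohort of recruited ED physicians". Appropriateness is judged on those referrals.

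The two parallel outcomes use a different multiplier. Outcome 4 (Radiation dose) uses "effective dose per scan X number of imaging avoided" and explains an avoided test as one where the "physician after consulting CDSS followed CDSS recommendations on not referring patient(s) for imaging". Outcome 5 (Sustainability) uses "carbon emissions/energy consumption X number of imaging avoided" and also states in its own text that volumes before and after implementation will be compared.

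**The concern.** A saving attributable to an intervention needs a count of what did not happen, or a difference between what happened with and without it. The Outcome 3 formula contains neither. It multiplies the unit cost by examinations that were ordered and judged inappropriate, which gives the cost that could still be removed.

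Cost avoidance is one of the five outcomes listed in the Introduction, and the Abstract promises an evaluation of the impact of the CDSS on it. The closing paragraph of the Limitations says the study will serve as evidence for adopting an integrated system locally. Followed literally, the plan would report a positive amount under the CDSS label even if the CDSS changed nothing. That amount would not correspond to the avoided dose and avoided carbon reported beside it.

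**Working it through.** The article states no cost-avoidance amount, so there is no figure to reproduce. The check is how the formula behaves as CDSS performance varies.

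**Inputs**
- Unit costs: EUR 68.22 cervical and EUR 79.85 lumbar (Outcome 3).
- Baseline inappropriate rate: 20% (Sample size).
- X-rays per phase: 235. This is borrowed from the Sample size section as a convenient volume. It is an assumption, because the article gives no expected number of examinations by body part.
- Case mix: unknown, so each result is a range from all cervical to all lumbar.
- Post-phase inappropriate rates of 30%, 20%, 10% and 0%: assumed.

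**Formulas**
- Plan: inappropriate X-rays × unit cost.
- Avoided cost at fixed volume: (inappropriate before − inappropriate after) × unit cost.

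At baseline, 235 × 0.20 = 47 inappropriate X-rays. At 10%, 235 × 0.10 = 23.5.

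**Count taken in the post-implementation CDSS phase**

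| Post-phase rate | Plan's formula (EUR) | Avoided cost (EUR) |
|---|---|---|
| 30% (worse) | 4,810 to 5,629 | −1,603 to −1,876 |
| 20% (no effect) | 47 × 68.22 = 3,206 to 47 × 79.85 = 3,753 | 0 |
| 10% | 23.5 × 68.22 = 1,603 to 23.5 × 79.85 = 1,876 | 1,603 to 1,876 |
| 0% | 0 | 3,206 to 3,753 |

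The two columns agree at 10% only because the assumed fall is exactly one half. Elsewhere they differ, and they move in opposite directions.

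The pattern does not depend on holding total volume fixed. If the 188 appropriate X-rays (235 − 47) are held fixed instead, a 10% rate means 188 × 0.10/0.90 = 20.9 inappropriate X-rays, and the plan's formula gives EUR 1,425 to 1,668.

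**Other choices of phase**
- Pre-phase only: EUR 3,206 to 3,753 whatever the CDSS does.
- Both phases pooled: 94 inappropriate X-rays, or EUR 6,413 to 7,506, with no effect. This falls to EUR 3,206 to 3,753 if the post-phase rate is 0%.

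Taken as a single product, the formula does not rise with CDSS benefit under any of these choices, and it is positive when there is no benefit.

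**The case against.** Three objections have weight.

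First, the section says *potential* cost avoidance. Read as cost that could be avoided, the product is coherent. This stands as a description of what the product measures. It does not make the product a CDSS result, which is how the sentence labels it. The next sentence, introduced as an addition, then promises the potential avoidance from inappropriate imaging. On this reading the two sentences repeat each other, and Outcome 3 contains no measure of what the CDSS achieved.

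Second, a before-after contrast is stated elsewhere. Comparator and intervention speaks of reviewing the difference between baseline and post-implementation results, and Data and statistical analysis applies a t-test to the outcomes before and after. If the product were computed in each phase and subtracted, it would move the right way: at fixed volume a fall to 10% gives (47 − 23.5) × unit cost = EUR 1,603 to 1,876. This stands as a remedy. Outcome 3 does not say so, however. It attaches the CDSS label to the undifferenced product, whereas Outcome 5 writes its before-after comparison into its own section.

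Third, Outcome 4 also reports the relative contributions of appropriate and inappropriate imaging to dose. The product therefore does have a dose counterpart. What is missing is the cost counterpart of avoided imaging.

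A reader might infer the stronger claim that the reported saving is necessarily largest when the CDSS fails and zero when it works perfectly. The documents do not support that. It requires the count to come only from post-implementation CDSS data, and the section names no phase or group.

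**Conclusion.** The concern holds in this form: the formula fixed for the CDSS cost avoidance measures the cost of inappropriate imaging that was ordered, and by itself does not measure cost avoided by the CDSS. It gives a positive figure with no CDSS effect. It falls as the CDSS improves if counted post-implementation, and is unrelated to the CDSS if counted in the pre-phase. It is also inconsistent with the multiplier in Outcomes 4 and 5.

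Under the stated assumptions, the amount wrongly credited to an ineffective CDSS would be EUR 3,206 to 3,753. The euro amounts are illustrative; the conclusion that the product is positive without any effect needs only some inappropriate imaging in the counted data.

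This is a secondary-outcome correction. The appropriateness analysis, recruitment and data collection are unaffected, and the matter can be put right at the analysis stage.

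**What to change.** In the Outcome 3 text:

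1. Define CDSS cost avoidance as unit cost × number of imaging tests avoided, by body part, using the definition of avoided imaging already given under Outcome 4. Outcomes 3, 4 and 5 then share one count, and the definitions in Outcomes 4 and 5 need no change.
2. Report as a separately labelled quantity the pre-to-post change in the cost of inappropriate imaging in the CDSS group minus the same change in the control group, with a confidence interval. This can differ from item 1, because it is a net change in ordered imaging and not a count of advice followed, so the two should not be merged.
3. Keep the present product, relabelled as the cost of inappropriate imaging (potentially avoidable), and state its phase and group. This also resolves the overlap with the sentence that follows it.

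The cost is a few sentences in one section. No new data are needed: the avoided count is already planned for Outcomes 4 and 5, and the inappropriate counts by phase and group are already collected for Outcome 1.

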#### Outcome 4: Radiation dose.

The established literature “Radiology: Patient Exposure from Radiologic and Nuclear Medicine Procedures in the United States: Procedure Volume and Effective Dose for the Period 2006–2016” will serve as the basis for estimating the radiation dose to patients [42]. The publication, based on the International Commission on Radiological Protection (ICRP) Publication 60, indicates an effective dose per scan of 0.36 mSv for X-rays of the Cervical Spine and 1.4 mSv for the Lumbar Spine. We will establish the cumulative effective dose associated with the imaging tests and highlight the comparison of the relative contributions of appropriate and inappropriate imaging with the total number of examinations and the total collective effective dose. We will also evaluate the number of imaging tests avoided (i.e., physician after consulting CDSS followed CDSS recommendations on not referring patient(s) for imaging) and the associated radiation dose prevented using the formula: “effective dose per scan X number of imaging avoided”.

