## Introduction

Diagnostic imaging has seen significant change over time. Since Wilhelm Conrad Roentgen’s discovery of X-rays, the field has evolved with the introduction of sophisticated equipment and new diagnostic imaging techniques, with many more emerging technologies, such as artificial intelligence, that will continue to change the way we acquire and process images [1]. Modern medicine relies heavily on diagnostic imaging, with clinicians perceiving it as a high-value tool with both clinicians and patients benefiting from the diagnostic insights provided by imaging procedures [2,3]. Diagnostic imaging embedded within the healthcare system plays a multitude of roles in the healthcare chain, such as prevention, detection, and diagnosis of diseases; delivery and monitoring of therapy; prognosis; and many others [4]. Indeed, with such a multitude of roles, the use of diagnostic imaging is increasing globally and is expected to rise more in the future [2,5,6].

However, heavy reliance on diagnostic imaging raises serious concerns. Economically, diagnostic imaging is expensive especially for advanced imaging techniques such as computed tomography (CT) and magnetic resonance imaging (MRI) [7]. In light of escalating healthcare expenditures and limited resources, the continued growth and demand of diagnostic imaging is unsustainable. Furthermore, there are potential negative ramifications for patients, such as the detection of benign incidental findings requiring further unnecessary workup, resulting in unwarranted patient anxiety from the aforementioned processes [8]. More importantly, some diagnostic imaging techniques, such as X-rays and CT, involve ionising radiation, which subjects patients to additional radiation exposure, making radiation protection a crucial aspect of the practice.

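### Outcomes 4 and 5 compute savings from spine X-rays alone, so a same-visit CT or MRI that replaces a dropped X-ray is neither detected nor subtracted

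*Protocol article*

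**What the plan says.** Outcome 4 (Radiation dose) rests on one published source, which "indicates an effective dose per scan of 0.36 mSv for X-rays of the Cervical Spine and 1.4 mSv for the Lumbar Spine". These are the only dose figures in the article. The outcome then defines what counts as avoided: "We will also evaluate the number of imaging tests avoided (i.e., physician after consulting CDSS followed CDSS recommendations on not referring patient(s) for imaging". Dose prevented is "effective dose per scan X number of imaging avoided".

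Outcome 5 (Sustainability) applies the same count to 0.91 kWh and 1.6 kg CO2e per spine X-ray. It adds a before-after comparison of spine referral volume, which it likens to the radiation outcome. It speaks of overall imaging use without naming modalities.

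The data collection text under Comparator and intervention limits the cohort to "consecutive patients referred to the ED’s radiology department for cervical and lumbar spine radiography by the cohort of recruited ED physicians". Table 1 gives criteria for cervical and lumbar X-rays only. The same section says that the CDSS stands alone and is not built into order entry, so physicians switch between two systems.

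The Introduction recognises that "some diagnostic imaging techniques, such as X-rays and CT, involve ionising radiation", but no later section mentions spine CT or MRI as something to record or subtract.

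**The concern.** The radiation rationale in the Introduction concerns the patient's exposure and later cancer risk. On that rationale, the quantity of interest is the change in the patient's dose from spine imaging. The formula in Outcome 4 gives something narrower: the X-ray dose that was not delivered. The two agree only if dropping an X-ray leaves all other spine imaging unchanged.

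If some physicians drop the X-ray and order a CT instead, the formula can still credit a full X-ray saving while an unrecorded CT dose is added. Energy and carbon have the same gap, and there an MRI would matter too. Radiation dose and sustainability are declared outcomes, and the Discussion says the study will serve as evidence for adopting an integrated CDSS. A gross X-ray figure read as a fall in patient dose could then mislead that decision.

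**Working it through.** The article predicts no dose saving, so there is no figure of its own to reproduce. The check uses its unit doses and its formula.

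**Inputs**
- x, dose per X-ray: 0.36 mSv cervical, 1.4 mSv lumbar (Outcome 4).
- Credited saving: x times the number avoided (Outcome 4).
- D, dose per spine CT: not in the documents; assumed 2 to 10 mSv.
- s, share of avoided X-rays replaced by CT: not in the documents.
- a, share of avoided X-rays that would otherwise have led to a follow-on CT: not in the documents.

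**Step 1. Credited saving per 100 avoided X-rays.** Cervical: 100 × 0.36 = 36 mSv. Lumbar: 100 × 1.4 = 140 mSv.

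**Step 2. One patient switched to CT.** The true change is D − x.
- Cervical: 2 − 0.36 = 1.64 to 10 − 0.36 = 9.64 mSv more.
- Lumbar: 2 − 1.4 = 0.6 to 10 − 1.4 = 8.6 mSv more.
- If D were only 1 mSv, a lumbar switch would lower dose (1 − 1.4 = −0.4 mSv). The sign therefore depends on an assumed figure.

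**Step 3. Net saving per 100 avoided X-rays.** Net = 100x − 100(s − a)D. With a = 0, the credited saving is cancelled at s = x/D.

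| Assumed D (mSv) | Cervical: cancelling share | Lumbar: cancelling share | Cervical: net at s = 10% (mSv) | Lumbar: net at s = 10% (mSv) |
|---|---|---|---|---|
| 2 | 0.36/2 = 18% | 1.4/2 = 70% | 36 − 20 = 16 | 140 − 20 = 120 |
| 5 | 0.36/5 = 7.2% | 1.4/5 = 28% | 36 − 50 = −14 | 140 − 50 = 90 |
| 10 | 0.36/10 = 3.6% | 1.4/10 = 14% | 36 − 100 = −64 | 140 − 100 = 40 |

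The cervical saving is the more fragile because its unit dose is small.

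**Step 4. The opposite direction.** Put s = 0 and, for illustration only, a = 10% with D = 5. The cervical net saving is then 36 + 50 = 86 mSv per 100, against 36 credited. X-ray-only accounting would understate the benefit.

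**Step 5. Can the data described supply s or a?**
- A patient whose X-ray was dropped was not referred for radiography, so falls outside the cohort.
- A session in a standalone CDSS shows the advice given, not what was ordered afterwards in the separate order-entry system.
- If the referral volume in the before-after comparison comes from the radiography cohort, each switch from X-ray to CT lowers it by one and looks like a reduction. Subtracting the control group's change does not remove switching that the CDSS itself causes.

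For energy and carbon the structure is the same. The article gives no CT or MRI values, so no break-even share is computed.

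**The case against.** The strongest reply is that the definition already excludes switched patients. It counts cases where the "physician after consulting CDSS followed CDSS recommendations on not referring patient(s) for imaging", and a patient sent for CT has been referred for imaging. This is a fair literal reading. A reader might infer that every switched patient is booked as dose prevented, and the wording does not support that. The booking follows only if imaging is read as spine X-ray, or through the before-after volume comparison. What remains is that the data described cannot verify the exclusion, for the reasons in Step 5 of the working.

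Four further points limit what can be said.
- **Direction.** A reader might infer that the error can only flatter the CDSS. It need not: the Introduction itself notes that imaging can trigger further workup, so an avoided X-ray may also avert a CT.
- **Likelihood of switching.** The high-risk trauma features in Table 1 might suggest that switching is common. In Table 1 those features make the X-ray appropriate, so such patients lie outside the avoided set. The recruited physicians work mostly with ambulant minor and non-emergency cases. The article never says that the CDSS redirects anyone to CT.
- **Data capture.** This is a condensed article. It mentions ED notes, imaging reports and follow-up to disposition. None of these amounts to capture of CT, especially for patients never X-rayed, but it would go too far to say that no CT information exists in the records.
- **Scope.** The study is openly about two X-rays, and these are associated outcomes presented as estimates. That is a reason to label the result narrowly. The Limitations discuss variation in unit dose, energy and carbon but not substitution.

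**Conclusion.** The point holds as a gap in accounting. Followed as written, Outcomes 4 and 5 report gross spine X-ray savings. They neither detect nor subtract spine CT or MRI that replaces a dropped X-ray in the same visit. Such a patient can be counted as a full saving.

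The size and direction of the error cannot be established from the documents. The cancelling shares of 3.6% to 18% (cervical) and 14% to 70% (lumbar) rest entirely on an assumed 2 to 10 mSv per spine CT and on no averted follow-on CT. They show sensitivity and do not predict what will happen. A reader might conclude that patients' dose will in fact rise; with neither a CT dose nor a switching rate in the article, that is not supported.

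The change is worth making because these are declared outcomes and the remedy is small. The primary outcome and the sample size do not depend on it.

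**What to change.** - From the same site's imaging orders, extract every spine CT and MRI ordered by the recruited physicians in the same ED visit, in both phases and both groups. Include visits with a CT or MRI but no X-ray.
- Count an X-ray as avoided only if no other spine imaging was ordered in that visit.
- Report the change in dose, energy and carbon net of all spine imaging, with cited unit values for CT and MRI beside the X-ray values already given.
- State which modalities the before-after volume comparison covers.

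If this is not done, label the results gross spine X-ray dose, energy and carbon, state that substitution was not measured, and do not conclude that patient dose fell.

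The cost is one further query of the same site's orders and a few more unit values. The reported saving may turn out smaller.
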